## Abstract

**Introduction:**

Chronic respiratory morbidity from bronchopulmonary dysplasia (BPD) remains the most common complication of preterm birth and has consequences for later respiratory, cardiovascular and neurodevelopmental outcomes. The early phases of respiratory illness are characterised by rapid consumption of endogenous surfactant and slow replenishment. Exogenous surfactant is routinely administered to infants born before 28 weeks of gestation as prophylaxis. Endogenous surfactant includes four proteins, known as surfactant proteins (SPs) A, B, C and D. Current bovine-derived and porcine-derived surfactant preparations only contain SPs B and C. SP-D has a key role in lung immune homeostasis as part of the innate immune system. Laboratory studies using recombinant SP-D have demonstrated reduced inflammation, which may be a pathway to reducing the associated morbidity from BPD. RESPONSE uses a recombinant fragment of human SP D (rfhSP-D), in a phase I safety and dose-escalation trial as the first stage in determining its effect in humans.

**Methods and analysis:**

This is a single-centre, dose-escalation, phase I safety study aiming to recruit 24 infants born before 30 weeks gestation with respiratory distress syndrome. In addition to routine surfactant replacement therapy, participants will receive three doses of rfhSP-D via endotracheal route at either 1 mg/kg, 2 mg/kg or 4 mg/kg. The study uses a Bayesian continual reassessment method to make dose escalation decisions. Dose-limiting events (DLE) in this trial will be graded according to the published Neonatal Adverse Event Severity Score. The primary outcome of this study is to evaluate the safety profile of rfhSP-D across each dose level based on the profile of DLE to establish the recommended phase 2 dose (RP2D) of rfhSP-D.

**Ethics and dissemination:**

The RESPONSE study has received ethical approval from London-Brent NHS Research Health Authority ethics committee. Results from the study will be published in peer-reviewed journals and presented at national and international conferences.

**Trial registration numbers:**

ISRCTN17083028, NCT05898633.

**Protocol version:**

RESPONSE Protocol V.4.0 24th July 2024.

STRENGTHS AND LIMITATIONS OF THIS STUDYThis study uses the International Neonatal Consortium Neonatal Adverse Event Severity Score (NAESS) which is specific to this population and allows a better grading and understanding of the adverse events and progression of the trial. This scoring system unlike others, for example, Common Terminology Criteria for Adverse Events takes into account age-appropriate behaviour, such as, feeding and physiological parameters. Although the NAESS has not been rigorously validated, it is well placed to improve the quality of drug evaluation in this highly vulnerable population.This is a safety study aiming to establish a recommended phase II dose of a novel therapy in a highly vulnerable population affected by Bronchopulmonary Dysplasia which has a significant impact on long-term lung health.This study uses Bayesian analysis which uses prior cohort data to inform the ongoing dose escalation.This is a single-centre study which may affect recruitment and the population characteristics.

## Introduction

### Clinical need for study

 The introduction of exogenous surfactant replacement therapy has significantly improved mortality in extremely preterm infants, those born before 28 weeks of gestation.^1^ Despite this, chronic respiratory morbidity from bronchopulmonary dysplasia (BPD) remains the most common complication of very preterm birth. BPD may be formally defined by the persisting need for respiratory support past 36 weeks postmenstrual age (PMA).^2^ It affects up to 75% of extremely preterm infants,^3^ with decreasing prevalence with increasing gestational age (GA).^4^ The pathogenesis of BPD is complex and multifactorial, involving lung immaturity, infection, inflammation, oxygen toxicity and ventilator-induced injury.

Unlike when first described, BPD is now rarely seen in infants born at more than 1200 g or after 30 weeks of gestation^2 5 6^ due to the introduction of antenatal steroid administration, surfactant replacement therapy, improved ventilation strategies and better nutrition.^7 8^ The prevalence of BPD has not fallen as expected.^8^,^10^ It can be argued that with advances in neonatal care leading to increased survival of infants at greatest risk of BPD, the prevalence may increase in years to come presenting a challenge for healthcare systems worldwide. Furthermore, BPD has lifelong consequences, with respiratory impairment that has important implications for adult clinicians, tracking through to adult life^11 12^ and neonatal BPD is also a marker for adult cognitive, educational and behavioural impairment with implications for health, wealth and relationships for life.^13^

As the mean GA of neonatal populations has fallen with increasing survival, the pathophysiology of chronic respiratory disease in very preterm populations has changed. Whereas the original descriptions of BPD related the occurrence and progression primarily to barotrauma from mechanical positive pressure ventilation,^14^ with increasing immaturity the profile of causation has changed, and this ‘new’ BPD^15^ is primarily found among extremely preterm infants. The primary driver in its development is lung inflammation, subject to the other risks referred to above. The disease is characterised by developmental arrest of lung tissue and a loss of alveolar septation by impairing alveolar crest development. This interruption in normal lung development with superimposed inflammation, oxygen toxicity and pressure-induced changes (barotrauma, volutrauma, atelectotrauma) completes the clinical picture.

Postnatal pulmonary inflammation is due to an imbalance in humoral factors favouring a proinflammatory response^16 17^ and increased presence of inflammatory cells in the airway.^18^ Inflammation, secondary to positive pressure ventilation, oxygen therapy or infection, may have a further impact on the cytokine profile and the interruption of lung development. The overwhelming evidence for inflammation as a causal mechanism in the development of BPD suggests that early anti-inflammatory therapies might reduce the frequency and severity of the condition. Identification of potential therapeutic targets remains a goal to reduce the frequency of BPD in high-risk infants. Naturally occurring surfactant proteins D (SP-D) has gained increasing interest as a potential immunotherapy to dampen the proinflammatory cascade and facilitate lung repair, thus reducing the frequency and severity of lung disease. In turn, this may have important long-term benefits for the child.

### Surfactant protein D

Mammalian surfactant comprises largely phospholipids (80%), neutral lipids (10%) and SPs (10%), dipalmitoylphosphatidylcholine being the primary surface-active component at the alveolar surface.^19^ Four SPs are found in surfactant, SP-A, SP-B, SP-C and SP-D. SP-B and SP-C are hydrophobic and their role is largely to stabilise the lipid monolayer formed at the air-liquid interface by stimulating phospholipid adsorption and reducing surface tension. Due to their hydrophobic nature, these SPs are easily extracted from bovine or porcine sources and present in widely used commercial surfactants. In contrast, SP-A and SP-D are hydrophilic and are not present in the surfactant preparations currently used in clinical practice.

SP-D is an essential lung component and functions to keep the lungs in a hyporesponsive state at rest, free from aberrant inflammation and infection. The actions of SP-D include aggregation of pathogens, antimicrobial activity against pathogens such as *Klebsiella,* increased phagocytosis and clearance of apoptotic cells and regulation of mediator production.^20^ SP-D consists of four main regions which include an N-terminal domain, a collagenous tail, a neck region and a carbohydrate recognition domain (CRD); it exists as a trimer. Through its carbohydrate recognition domain, SP-D binds carbohydrates in a calcium-dependent manner^20 21^ and via the N-terminal region, the trimeric units oligomerise to give rise to a dodecameric cross-like structure. These can further form oligomers or ‘stellate multimers’, which increase the strength to bind carbohydrates and agglutinate various pathogens.^20^

### SP-D levels in preterm infants and evidence for recombinant fragment SP-D as a therapeutic agent

Bronchoalveolar lavage (BAL) samples taken from preterm infants over the first few days after birth have demonstrated low concentrations of SP-D in association with respiratory distress syndrome (RDS) that were associated with an increased risk of BPD.^22 23^ Binding assay studies evaluating the lectin activity of SP-D demonstrate that the SP-D present in the BAL of preterm infants was less effective than that in term infants.^23^ Sepsis in preterm infants can be life-threatening and contributes significantly to the inflammation seen in BPD. Further, SP-D concentrations increase in preterm infants in the presence of sepsis, demonstrating its potential role as an acute phase reactant.^24^ Given the known interactions of SP-D with bacterial, viral and fungal pathogens,^20 25^ intervention with SP-D would be expected to promote their clearance in this vulnerable population and reduce further damage. Finally, in SP-D knock-out mouse models,^26^ emphysematous changes are seen that are similar to those seen in the lungs of preterm infants.

Given these homeostatic and anti-inflammatory roles of SP-D, it is an attractive target for therapy, and if administered early to preterm infants there would be a reduction in inflammation by downregulation of the proinflammatory signalling pathways in addition to interaction with common pathogens that induce inflammation such as *Escherichia coli.* In vivo studies in preterm lambs given recombinant full-length SP-D in addition to commercially available surfactant showed a clear reduction in the proinflammatory cytokines such as interleukin-8 (IL-8),^27^ which provides encouraging data for its potential clinical use in this population.

In practice, the properties of full-length SP-D (including varying degrees of oligomerisation, limited solubilisation and potential aggregation at higher concentrations) make it difficult to develop a stable preparation that could be administered. Therefore, recombinant fragments of human SP-D have been explored in translational models as a potential therapy for BPD. Preclinical data showed the efficacy of rfhSP-D treatment in reducing and correcting inflammation in chronic inflammatory lung disease caused by SP-D deficiency. SP-D knock-out mice develop symptoms of chronic obstructive pulmonary disease and emphysema relevant to BPD, which are correctable following treatment with recombinant SP-D.^26 28^

A stable form of rfhSP-D has been produced using a mammalian cell line and purified using affinity chromatography using a N-Acetylmannosamine (ManNAc)-coupled matrix as described previously.^29^ The recombinant fragment comprises the neck, CRD and eight gly-Xaa-Yaa repeats similar to that described for a bacterially expressed recombinant fragment of human SP-D.^30^ The CRD is the functional anti-inflammatory and anti-infective part of the protein without the long collagenous tail and the suggested proinflammatory N-terminal region.^30^ The rfhSP-D proposed as an investigational medicinal product (IMP) retains its anti-inflammatory properties when used as an adjunct to exogenous surfactant therapy administered via an endotracheal tube in a well-established translational model using preterm ventilated lambs.^31^ The endotoxin content is less than 0.05 EU/mg rfhSP-D.

### Justification for the dosage regimen in the safety trial

The proposed regimen is based on the estimation of human equivalent dosages based on effective dosing in animals. In murine studies, the replacement dose of rfhSP-D was 10 µg daily. Assuming an average mouse weight of approximately 10–20 g, this approximates to 1–2 mg/kg per day. The effective dose of rfhSP-D in the preterm lamb has been estimated to be 1.5 mg/kg (unpublished data). In current practice, the administration of 100–200 mg/kg of surfactant replacement would contain 1–4 mg/kg if a naturally occurring product was used. Hence, after due consideration, we elected to trial three potential dose levels of rfhSP-D, namely 1, 2 and 4 mg/kg/dose.

### Study objectives

RESPONSE is a phase I study and aims to assess the safety of 3 intratracheal dose levels (1 mg/kg/dose, 2 mg/kg/dose and 4 mg/kg/dose) of rfhSP-D in preterm ventilated infants (23 weeks - 29 weeks and 6 days) at risk of BPD.

The primary objectives are as follows:

To assess the safety profile of rfhSP-D across three dose levels based on the occurrence of dose-limiting events (DLEs) as defined below.To establish the recommended phase 2 dose (RP2D) of rfhSP-D for preterm infants born before 30 weeks of gestation.

Secondary objectives are as follows:

To evaluate systemic absorption of rfhSP-D using serial measurements of SP-D in plasma and its continued presence in tracheal fluid.To determine the effect of rfhSP-D on inflammatory markers in lung secretions and plasma (eg, cell counts of neutrophils, macrophages, lymphocytes and cytokine; IL-8, IL-6, IL- 1).To compare the clinical effects of intratracheal administration of rfhSP-D on physiological and intensive care parameters in treated infants in this trial with non-treated infants from a parallel observational cohort study of untreated infants.

## Methods and analysis

### Trial design

The study will be conducted in a single-centre, tertiary level 3 neonatal intensive care unit. The study was opened on 6 February 2024 and has a proposed 12-month recruitment period. We aim to recruit 24 infants born between 23 weeks+0 days and 29 weeks+6 days gestation. To date, four infants have been recruited to the study. This study uses a Bayesian continual reassessment model (CRM),^32^,^34^ a model-based design that informs how the dosage of rfhSP-D should be adapted for the next participant cohort based on past trial data. For this first-in-human study, a dose escalation design will be used (figure 1).

**Figure 1 F1:**
[figure not shown]
Dose escalation process in RESPONSE using rfhSP-D in preterm infants at risk of BPD. *Via Endotracheal tube only. **First iteration will be at 1mg/kg/dose, subsequent iterations 2 mg/kg/dose and 4 mg/Kg/dose. ***Neonatal Adverse Event Severity Score (NAESS). ****administration window of +2 hours. BPD, bronchopulmonary dysplasia; DLE, dose-limiting event; DSMB, data and safety monitoring board; TSC, trial steering committee.

The three dose levels to be considered are 1 mg/kg/dose, 2 mg/kg/dose and 4 mg/kg/dose. Participants will be enrolled at each dose level with a minimum of three participants per dose level. Each participant will receive three doses of rfhSP-D at 0 hours, 12 hours and 24 hours provided that they continue to meet the inclusion criteria and are clinically stable. The first dose of rfhSP-D should be administered after standard surfactant therapy has been given. Whether or not the dose level is escalated will depend on the occurrence of DLEs in all current participants and the doses they have received. A model will be used to estimate the risk of DLE per dose level. Initial estimates of these risks will be updated using data collected throughout the trial. A one-parameter empiric model will be used to describe the relationship between the dose and the probability of observing a DLE. The CRM model will not allow dose-skipping. The target level of DLEs level is set at no greater than 20%. Before the trial, the parameter of the model will be assigned a non-informative prior distribution and initial estimates of DLE probabilities will be derived using model calibration. The recommended phase 2 dose will be defined by considering safety and will be the highest dose level that has an estimated probability of DLE closest but below the target DLE level of no greater than 20%.

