### Data collection and management

Participants once recruited to the RESPONSE study will be allocated a study number so that all data and samples that are taken are anonymised, for example, RES_001. Participation in the clinical study will be recorded in the participant clinical records. Participants will be enrolled by the study team on the OpenClinica database. Participant clinical and laboratory data will be entered directly into the password-protected study database. After completion of the trial, the data will be exported and retained in restricted folders by the sponsor. All data will be held for 10 years following the completion of the trial.

Primary outcome data collection in this study (safety profile of rfhSP-D) will be done through grading and analysis of the incidence of DLEs. Potential causality of the DLE to the IMP will be assessed by an independent neonatologist. In addition to the DLEs, the following datasets will be collected from electronic patient records:

At screening and on eligibility assessment: sex of participant, ethnicity, maternal medical history, antenatal steroid courses, date and time of rupture of membranes, concerns about maternal sepsis, ventilatory requirement on admission and administration of standard exogenous surfactant.

Secondary outcome data collection:

Data will also be collected at the time points specified in the schedule of events (tables2  3) and this will include concomitant medication, ventilatory support and parameters, known positive microbiology, use of postnatal steroids, presence and treatment of pulmonary hypertension, pneumothorax, patent ductus arteriosus, use of postnatal steroids.At 36 weeks, PMA all participants will be assessed for severity of BPD and data will be collected about complications of prematurity such as episodes of necrotising enterocolitis and retinopathy of prematurity. The severity of BPD in participants will be defined as per the 2019 National Institute of Child health and Development (NICHD) criteria,^36^ an oxygen reduction test will be done if the participant is eligible (requiring less than Fi02<0.3 or 1.1 L/min and not on positive pressure support) and remains an inpatient at the recruiting site.

**Table 3 T3:** Operating characteristics of the continuous reassessment model

Starting dose level 1, dose-skipping not allowed, 3 dose levels, maximum 24 participants.Skeleton (a priori probabilities of DLE) = 0.05, 0.11, 0.20target DLE rate=no greater than 20%			

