### Sample size and statistical analysis

As this is a safety study, no formal sample size calculation has been performed. A sample size of 24 infants is planned to meet practical recruitment and time targets and to collect sufficient data to quantify the estimated risk of DLE at each dose level. Participants with unclear safety outcomes or who have not started study treatment will be replaced to meet our planned effective sample size of 24 participants.

The primary outcome of interest is the occurrence of DLEs at the dose levels under investigation and the identification of the dose(s) that, for infants of particular risk profiles defined by GA, have an estimated risk of DLE closest to the target side effect level of no greater than 20%. The use of Bayesian methodology to estimate risks will allow information to be borrowed across dose levels, making the dose-escalation and RP2D identification procedure more efficient than a standard rule-based approach.

The operating characteristics of the design, for three specific scenarios, are shown in table 3. The first scenario is one where the initial a priori DLE probabilities calculated by calibration (halfwidth of the indifference interval set at 0.05) correspond to the true underlying probabilities of DLE. The second scenario is such that the true DLE rate of the second dose level corresponds to the target DLE rate. The third scenario is one where the true probabilities are much lower than the a priori probabilities.

Type and grade of DLEs, SAEs and AEs will be tabulated per dose level, and further summarised by risk group defined by GA. Mean estimated risk of DLE per dose level and 95% credibility intervals will be calculated using the study model. Secondary objectives will be described per dose level and risk category. Categorical variables will be summarised by frequencies and percentages, and continuous variables by means/medians and SD/IQRs per dose level.

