#### Interim analyses of DLEs

Interim analysis will done to assess if DLEs have occurred after each infant (for the first three participants at each dose level) has received the final dose of IMP and 72 hours of monitoring and all NAESS data will be reviewed by the DSMB. The DSMB will evaluate the safety data before further participants can be recruited, this will only be for the first three infants at each dose level. The purpose of this is to ensure there are no safety concerns. For the remainder of the study, interim analysis will be done after cohorts of three participants are recruited at any dose level to assess the occurrence of DLE and review all clinical data. Overall DSMB review of all data to advise the TSC regarding dose escalation will take place after recruitment of 3 infants at any dose level. The trial statistician will calculate and provide updated summaries of the estimated risk of dose-limiting toxicity at each dose level. The DSMB will then advise if dose escalation can occur. There will be no interim analysis for the secondary outcomes.

The study will be terminated if any of the following stopping rules are satisfied:

There is at least a 90% chance that the risk of DLE at dose level 1 is greater than the target of 20%. If the trial is terminated under this rule, no drug dose will be recommended due to safety concerns.The number of participants who have been treated without side effects is deemed sufficient.There is evidence of increased mortality or morbidity in the participants treated with the IMP.

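### The RP2D rule is worded two ways, and Table 3 matches the 'closest to 20%' wording, not the 'closest but below' definition under Trial design

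*Protocol article*

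**What the plan says.** All references are to the protocol article.

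- **Trial design (text below Figure 1).** The RP2D is "the highest dose level that has an estimated probability of DLE closest but below the target DLE level", and the target is fixed by "The target level of DLEs level is set at no greater than 20" per cent. The model is a one-parameter empiric continual reassessment model (CRM), and "the parameter of the model will be assigned a non-informative prior distribution".
- **Sample size and statistical analysis.** The primary outcome includes identifying the dose or doses that "have an estimated risk of DLE closest to the target side effect level of no greater than 20" per cent. There is no requirement to be below. The same section presents Table 3 as the design's operating characteristics.
- **Table 3.** Conditions: "Starting dose level 1, dose-skipping not allowed, 3 dose levels, maximum 24 participants", with skeleton 0.05, 0.11, 0.20. It gives recommendation percentages for levels 1 to 3 in three scenarios. It does not say which RP2D rule was used or whether stopping was applied.
- **Interim analyses of DLEs.** The trial stops if "There is at least a 90% chance that the risk of DLE at dose level 1 is greater than the target of 20" per cent, and no dose is then recommended.

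**The concern.** Establishing the RP2D is one of the two primary objectives. When the estimate nearest to 20% lies just above it, the closest rule takes that dose and the below rule takes a lower one.

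The skeleton shows how easily this happens. If the fitted exponent were 0.94 (an illustrative value), the estimates would be 0.05^0.94 = 0.060, 0.11^0.94 = 0.126 and 0.20^0.94 = 0.220. Level 3 is 0.020 from the target and level 2 is 0.074 from it. The closest rule picks level 3; the below rule picks level 2.

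If Table 3 was computed under one wording while the definition uses the other, those overseeing the trial are looking at selection probabilities for a different rule. If the table leaves out stopped trials as well, it says nothing about the one stopping rule that has a numerical threshold.

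**Working it through.** **Inputs from the article.** Empiric model, target 0.20, skeleton 0.05/0.11/0.20, "halfwidth of the indifference interval set at 0.05", start at level 1, no skipping, 24 participants, review in cohorts of three, the three true-risk scenarios of Table 3, and the 90% stopping rule.

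**Assumed.** The article gives no prior variance. The base case takes β ~ N(0, 1.34), with 0.5 to 4 as the range. Risk is estimated by plugging in the posterior mean of β.

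**Step 1: the skeleton.** For an empiric model with half-width 0.05 and level 3 set at the target, ln p(k) = ln(0.15) × ln p(k+1) / ln(0.25).

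- Level 2: −1.897 × −1.609 / −1.386 = −2.203, so p = 0.111.
- Level 1: −1.897 × −2.203 / −1.386 = −3.014, so p = 0.049.

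This matches 0.05/0.11/0.20, so the calibration is understood correctly.

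**Step 2: the trial model.** p(k) = skeleton(k)^exp(β). The posterior is proportional to the prior times the product over levels of p(k)^y(k) × (1 − p(k))^(n(k) − y(k)). All paths through eight cohorts of three were enumerated with binomial weights, so there is no simulation error.

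**Step 3: results, base case, in per cent.** In the last two rows the same rule is used for allocation and for the final choice.

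| | Scenario 1: level 1 / 2 / 3 | Scenario 2: level 1 / 2 / 3 | Scenario 3: level 1 / 2 / 3 |
|---|---|---|---|
| Table 3 | 2.5 / 24.5 / 73.0 | 22.5 / 46.5 / 31.0 | 0.0 / 3.3 / 96.7 |
| Closest, stopping not applied | 2.4 / 23.7 / 73.8 | 21.5 / 47.3 / 31.2 | 0.1 / 2.7 / 97.3 |
| Below, 90% rule applied | 8.7 / 41.3 / 48.8 | 34.4 / 42.8 / 13.3 | 0.6 / 10.6 / 88.7 |

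The second row is within 1.0 point of Table 3 in every cell. The third misses Scenario 1 level 3 by 73.0 − 48.8 = 24.2 points and Scenario 2 level 3 by 31.0 − 13.3 = 17.7 points.

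There is a simple reason. In Scenario 1 the true level 3 risk equals the target, so its estimate falls below 20% in roughly half of trials. A below rule cannot be expected to reach 73%.

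**Step 4: sensitivity.** With prior variance 0.5 to 4, and either rule for allocation during the trial, a below final rule with stopping gives level 3 in about 49–52% (Scenario 1) and 13–15% (Scenario 2). Other priors, cohort schemes and risk estimators were also tried. In every variant with a below final rule, at least one cell was off by 14.6 points or more. The final selection rule drives the gap; the allocation rule matters little.

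**Step 5: no-dose outcomes.** Table 3's rows each sum to 100.0: 2.5 + 24.5 + 73.0, 22.5 + 46.5 + 31.0 and 0.0 + 3.3 + 96.7. In the base case the 90% rule stops 0.9%, 4.1% and 0.1% of trials in Scenarios 1, 2 and 3.

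**Step 6: what is not tested.** True level 1 risks in Table 3 are 0.05, 0.10 and 0.02, all under 0.20. As an illustration outside the table, take true risks 0.30/0.40/0.50 in the base case. The 90% rule stops about 58% of trials. The closest rule still names a dose in about 42%. The below rule does so in about 14%, if no dose is named when none is estimated below 20%.

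**The case against.** **The second wording may be loose shorthand.** The statistical section describes the primary outcome, and its target is itself expressed as an upper limit. Only the Trial design section says how the RP2D will be defined. That reading is fair and softens the contradiction in the text. It does not rescue Table 3: if below is the intended rule throughout, the table does not describe it.

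**The prior is unknown.** True, but no prior that was tried closes the gap.

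**A reader might infer that Table 3 can be obtained only with the stopping rule switched off.** The calculation does not show that. With stopping on, the cells also fit within 1.2 points if stopped trials are counted as level 1, and within 1.6 points if stopped trials are excluded and at least three infants are required per level before escalation. Neither treatment matches the stated consequence of a stop. The evidence on stopping is the absence of any no-dose outcome, and its effect in these scenarios is small.

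**A reader might infer that an early DLE at level 1 leaves the trial without instructions**, with no dose estimated below 20% and the 90% rule not met. The documents do not support this. The sentence at issue defines the RP2D, not interim allocation. The dose escalation procedure and the Figure 2 legend give interim decisions to the DSMB and TSC. The example also depends on the prior: after 1 DLE in 3 infants the level 1 estimate is about 0.18, 0.27 or 0.35 at variance 0.5, 1.34 or 4. What remains open is the end-of-trial outcome when no dose meets the rule.

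**Further scenarios may sit in the full protocol.** Possibly. That tempers the request for a toxic scenario, but not the mismatch in the published table.

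**Conclusion.** The concern stands. Two wordings of the RP2D rule can select different doses, and Table 3 matches the closest-to-target wording and not the definition under Trial design. The size is about 73% against 49% for level 3 in Scenario 1, and 31% against 13% in Scenario 2. This rests on the assumed normal prior (variance 1.34) and cohorts of 3, and is stable for variance 0.5 to 4.

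Two limits apply. The Scenario 1 drop should not be called a loss of correct selection: level 3's true risk there is exactly 0.20, so under a literal below rule it is not clearly the right dose. Nor should all no-dose outcomes be put down to the stopping rule. In Scenario 2 about 4.1% are formal stops. The total reaches about 9.5% only if, in addition, no dose is named when none is estimated below 20%, a convention the article does not state.

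The missing no-dose outcome is a smaller fault, worth about 1%, 4% and 0.1% of trials in the three scenarios. The table gives no information on how the 90% rule performs when level 1 is too toxic.

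**What to change.** 1. Reconcile the Trial design and sample size sections to one RP2D rule. The choice is the sponsor's. State the end-of-trial outcome if no dose meets it.
2. Regenerate Table 3 under that rule with the 90% stopping rule applied. State the prior, the cohort scheme and the rule used.
3. Add a column for no dose recommended and one scenario with the level 1 risk above 20%.
4. If the closest rule is kept, correct the Trial design definition, because the selected dose may then have an estimated risk above 20%.

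The cost is a wording amendment and a short re-simulation. The selection percentages may look less favourable. The article reports that recruitment has begun, with four infants enrolled, so the rule should be settled before any RP2D is named.
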